#### Assessments

Measures are conducted at baseline (month one) and post-treatment (month
9).

#### Anthropometric measures

Weighing electronic scales with a maximum capacity of 150 kg and precision of
100 g, properly checked for tare weight, will be used for weight measures.
The individual will be weighted barefoot and wearing light clothes. A
metallic measuring tape with a capacity of 2 m/0.1 cm, set in an existing
flat wall in the room, will be used to measure height, with the individual
in the upright position, during maximum inspiration, barefoot and with empty
pockets. These data will be used for the following calculation of BMI,
obtained by weight, measured in kilograms, divided by the square of the
height, measured in meters (kg/m^2^). That will be calculated and
nutritional status will be classified, both using the *Anthro
Plus* software, according to the reference of the World Health
Organization (WHO) 2006/2007.

#### Dietary intake

The collection of dietary data, referring to the eating habits of the
participants, will be assessed by a Food Frequency Questionnaire
(FFQ),^20^
previously validated for the study population, designed to collect
information on the frequency of food consumption and/or food groups for
further association with other study variables, such as lifestyle and
anthropometric measurements.

#### Physical activity

International Physical Activity Questionnaire (IPAQ)^21,22^ will be used for all ages to classify the level of
physical activity, in spite of the fact this instrument has being validated
only for adults and adolescents, since there is not yet a validated
questionnaire that can suit the needs of this study and adequately classify
physical activity levels in Brazilian children.

#### Screen Time

Screen time refers to the amount of time individuals spend in front of
television, video games and computer, and is considered to be a sedentary
activity. It will be measured by hours per day and number of days in the
week of screen time.

#### Knowledge of healthy habits

The acquisition of knowledge about healthy habits will be evaluated through a
questionnaire validated for age,^23^ consisted of knowledge about food and healthy
activities in daily life.

#### Demographics measures

During baseline assessment, parents will be asked about a series of
demographic data included in the Brazilian Economic Classification Criterion
by the Brazilian Association of Research Companies,^24^ which includes: age;
educational attainment of the family head; questions about household
appliances and other family properties; street paving and treated water in
the house.

#### Sample size

The sample size was calculated to detect a difference in 0.2 kg/m^2^
on BMI, with a standard deviation of 0.05, statistical power of 90% and
alpha error of 0.05. An estimate of mean 19 kg/m^2^ is used as
obtained from our pilot study. A number of 99 participants per group was
estimated using these parameters. To compensate for losses, the sample size
will be increased by 10%.

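### The stated sample-size inputs give about 3 children per group, not 99, so at least the standard deviation or the difference is misstated

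*Protocol article*

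**What the plan says.** The Sample size section of the protocol article opens: "The sample size was calculated to detect a difference in 0.2 kg/m^2". It continues "on BMI, with a standard deviation of 0.05, statistical power of 90% and alpha error of 0.05". A pilot value follows ("An estimate of mean 19 kg/m^2^ is used"), and then the result: "A number of 99 participants per group was estimated using these parameters". A 10% increase for losses is applied after that.

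The Study design section names change in BMI as the primary outcome. The Randomization section allocates two schools to each arm. The Sample size section gives no intracluster correlation, no design effect and no statement of one- or two-sided testing.

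**The concern.** The paragraph ties its inputs to its result explicitly, so it can be checked on its own terms. A difference four times the standard deviation would need only a handful of children, yet the paragraph arrives at 99 per group.

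This is the only planning statement for the primary outcome. If its inputs do not produce its answer, a reader cannot tell what difference the trial was built to detect, or with what power. A null result would be read against a 90% claim that the paragraph does not support as written.

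**Working it through.** **Inputs** (all from the Sample size section): difference 0.2 kg/m²; SD 0.05; power 90%; alpha 0.05. Two-sided testing is assumed because sidedness is not stated. The pilot mean of 19 kg/m² does not enter a comparison of two means.

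**Formula:** n per group = 2 × (z for alpha + z for power)² × (SD / difference)².

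**Attempt to reproduce 99 from the stated inputs**
- Normal formula: 2 × (1.960 + 1.2816)² × (0.05 / 0.2)² = 21.015 × 0.0625 = 1.31.
- Two-sample t-test (noncentral t): power is 56.5% with 2 per group and 94.8% with 3, so 3 per group.
- With 99 per group and these inputs, power would be essentially 100%.

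**Other readings of the stated inputs**
- One-sided alpha: 2 per group (normal) or 3 (t).
- 0.05 read as a variance: 21.015 × 0.05 / 0.04 = 26.3, so 27.
- 0.05 read as 5% of the mean (SD 0.95): 21.015 × (0.95 / 0.2)² = 474.2, so 475.
- Loss allowance: applied after the 99, so it cannot explain it.
- An unstated design effect: 99 / 3 = 33. With about 49.5 children per school, this needs an intracluster correlation of (33 − 1) / 48.5 = 0.66. Starting from 1.31 instead, the design effect is 75.4 and the correlation would have to be 1.53, which is impossible.
- A different power alone: at SD 0.05, the usual levels of 80%, 90% and 95% give at most 4 per group, even by the t-test.

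**Combinations that do give 99 by the normal formula**

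| Difference | SD | Power | n per group |
|---|---|---|---|
| 0.2 | 0.434 | 90% | 21.015 × (0.434 / 0.2)² = 99.0 |
| 0.2 | 0.5 | 80% | 2 × (1.960 + 0.8416)² × 6.25 = 98.1, up to 99 |
| 0.02 | 0.05 | 80% | same ratio of 2.5, 98.1, up to 99 |
| about 0.023 (0.02304) | 0.05 | 90% | 21.015 × (0.05 / 0.02304)² = 99.0 |

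The t-test shifts these slightly: SD 0.5 at 80% power then needs 100, and 99 at 90% power corresponds to SD of about 0.43.

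**What one reconstruction would imply (illustration only): SD 0.5, difference 0.2**
- Power with 99 per group, before clustering: Φ(0.4 × √49.5 − 1.960) = Φ(0.854) = 80%.
- Needed for 90% power: 21.015 × 6.25 = 131.3, so 132 (133 by the t-test).
- Difference detectable at 90% power with 99 per group: 3.2416 × √(2 / 99) × 0.5 = 0.23 kg/m².
- Allowing for schools, with an assumed intracluster correlation of 0.01 to 0.05: the design effect is 1 + 48.5 × 0.01 = 1.485 to 1 + 48.5 × 0.05 = 3.425. Power is then Φ(2.814 / √1.485 − 1.960) = 64% down to Φ(2.814 / √3.425 − 1.960) = 33%. This still ignores the few degrees of freedom that four schools leave, so it is optimistic.

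**The case against.** The best defence is that this is a slip in print and that the real calculation was sound. If the SD used was about 0.434, the stated 90% power holds under individual randomisation and only one figure needs correcting. Nothing in the article excludes that. It limits what can be said about the consequences, but it leaves the contradiction in place, because the printed inputs still do not give the printed number.

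Three stronger readings are tempting, and the article does not support them.

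- A reader might infer a misplaced decimal (SD 0.5) together with a true power of 80%. It fits, but it needs two errors in one sentence, whereas SD of about 0.434, or a difference of about 0.023, needs only one. The fit also depends on method, since the t-test gives 100 rather than 99.
- A reader might conclude that the error must lie in the SD or the power. Power alone cannot explain 99, and the difference may itself be the misprint.
- A reader might say that an SD of 0.05 is impossible for BMI in children, or that the trial is far less sensitive than claimed. The article reports only a pilot mean and no observed SD. The first is a judgement that the arithmetic does not need, and the second depends on which input was wrong.

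**Conclusion.** The paragraph is wrong as written. Its inputs give about 3 children per group (1.3 by the normal formula), so the stated 99 is roughly 33 times what they require. This rests only on the printed figures and holds for one- or two-sided testing.

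At least the SD or the difference is misstated, and the power may be as well. The article does not show which, so it does not establish that true power is below 90% before clustering. The 80% figure applies only if the SD was 0.5. Separately, every reconstruction here treats children as individually randomised, so none of them gives the power of a trial that randomises four schools.

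**What to change.** Return to the pilot data and the original calculation. Restate three figures together so that they reproduce 99: the SD of the primary outcome (change in BMI), the difference, and the power. State whether alpha is one- or two-sided.

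Then give the power, or the detectable difference, that 99 per group provides with the corrected SD. Label it as before clustering, and put beside it a figure that allows for two schools per arm, with the assumed intracluster correlation stated. An individually randomised figure should not stand alone as the power of this trial.

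The cost is one corrected paragraph, and the stated power or detectable difference may become less favourable. No extra enrolment is needed if the claim is restated. If the SD proves to be 0.5 and 90% power is to be kept, 132 to 133 per group would be needed before losses and clustering.

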#### Planned data analyses

Collected data will be entered and analyzed using the Statistical Package for
Social Sciences, version 17.0. Quantitative variables will be expressed as
mean and standard deviation in the presence of normal distribution or median
and interquartile range in the presence of asymmetric distribution.
Qualitative variables are expressed as absolute and relative
frequencies.

Adjusted analysis for primary and secondary outcomes will be performed using
generalized estimating equations (GEE). The comparison between secondary
outcomes will be performed using the nonparametric Wilcoxon test.

The level of significance for all tests will be 95% (α = 0.05) and
will follow the intention to treat principle. P-values will be reported up
to three decimal places with p-values < 0.005 reported as p < 0.005.
The outcomes will be evaluated by a blind adjudicator.

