### Study design

#### Overview

This is a cluster-randomized parallel two-arm study conducted in Brazil. The
units of observation are individual children, and the units of randomization
are schools. Randomization will be performed at the school level to avoid
contamination. After the baseline assessment, enrolled schools are
randomized to one of two study arms: the intervention arm focusing on
changes in lifestyle, and the control group arm, that receives usual
recommendations by the health care team. A summary of the study design,
interventions and timelines is shown in Figure 1.

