**Figure 1 f1:**
[figure not shown]
Flowchart of the study phases (enrolment, intervention
allocation, and fnal assessments).

The primary outcome for the participants is change in body mass index (BMI =
kg/m^2^), and the secondary outcomes are behaviors related to
healthy eating, increased preferences for fruits and vegetables, increased
physical activity and reduced screen time. The Institutional Research Ethics
Committee approved the protocol for the study, which is registered in the
Brazilian Registry of Clinical Trials, Register Number RBR-97bztb, and named
“Intervention program for health promotion in schools of public elementary
school in the state of Rio Grande do Sul: randomized clinical study”. The
Universal Trial Number of this study is U1111-1155-7731.

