#### Randomization

Cluster randomization will be performed with distribution of two schools for
the control group and two schools for the intervention group. A
biostatistician who does not have direct contact with study participants
will generate the random allocation sequences using a computerized random
number generator. After the inclusion of each cluster, the allocation of
that particular cluster will be provided to the study coordinator. Due to
the characteristics of the intervention, it is not possible to mask
participants or interventionists to group assignment. There will be no
crossover between study arms, but the intervention will be offered to the
control group at the end of the study, if proved to be effective.

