#### Usual care comparator

Participants randomized to the control group will not receive any guidance
during the study. Children will receive the usual care and recommendations
through the school and health authorities.

Should the intervention prove to be effective, at the end of the study, the
institutions allocated to the control group will receive all intervention
activities if they wish.

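### With four randomised schools, standard GEE does not hold the stated 0.05 error rate: about 30% two-sided if grouped by school, 5% to 30% if grouped by child (assumed ICC 0 to 0.05)

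*Protocol article*

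**What the plan says.** The Overview of the protocol article separates the two levels: "The units of observation are individual children, and the units of randomization are schools". The section on Randomization fixes the number of clusters: "Cluster randomization will be performed with distribution of two schools for the control group and two schools for the intervention group". The primary outcome is set in the text after Figure 1: "The primary outcome for the participants is change in body mass index (BMI = kg/m^2").

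Planned data analyses names the method for primary and secondary outcomes, "Adjusted analysis for primary and secondary outcomes will be performed using generalized estimating equations (GEE"), and the threshold, "The level of significance for all tests will be 95% (α = 0.05"). The software is SPSS 17.0. The article does not say whether GEE groups by school or by child. It also does not give the variance estimator, any few-cluster correction, the reference distribution or whether the test is two-sided.

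The Sample size section derives 99 children per group at 90% power, plus 10% for losses. It mentions no ICC or design effect.

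**The concern.** The robust variance in GEE is justified as the number of independent clusters becomes large. Here the treatment effect is a contrast of two schools with two schools, so the between-school variance is estimated with 2 degrees of freedom. A default GEE analysis compares the result with 1.96 as if that variance were known. If GEE is instead grouped by child, to link the baseline and month-9 measurements, any correlation between pupils of the same school is left out.

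At stake is the reported p-value for the primary outcome, and for any secondary outcome analysed in the same way. The protocol's stated aim is to test effectiveness before wider use, and the comparator section opens a further step with "Should the intervention prove to be effective, at the end of the study". A test that rejects several times too often under no effect cannot support such a statement.

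**Working it through.** **Inputs.** From the documents: 2 schools per arm (Randomization); GEE and alpha 0.05 (Planned data analyses); 99 children per group plus 10%, so about 109 per group or 54 per school, a 0.2 kg/m² difference and 90% power (Sample size). Assumed, because not stated: two-sided testing, similar school sizes, ICC values from 0 to 0.05, and the SD in step 5.

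**1. The plan's own sample size.** n per group = 2(1.960 + 1.282)²(SD/difference)². With the stated SD of 0.05 and difference of 0.2 this is 2 × 10.51 × 0.0625 = 1.3, which rounds up to 2, not 99. The figure of 99 is reproduced at 90% power with SD 0.434: 2 × 10.51 × (0.434/0.2)² = 99.0. It is also reproduced with SD 0.5 at 80% power. This is a separate matter and steps 2 to 4 do not depend on it. The SD of 0.434 is used only in step 5.

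**2. GEE grouped by school.** With k equal-sized schools per arm, the estimated effect is the difference between the arm averages of the school means. The uncorrected sandwich variance is (k − 1)/k times the unbiased between-school estimate, which has 2k − 2 degrees of freedom. For k = 2 it is on average half the true variance, so the Wald statistic is √2 × t on 2 df.

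- Type I error = P(|t₂| > 1.96/√2) = P(|t₂| > 1.386).
- For 2 df, P(|t₂| > c) = 1 − c/√(2 + c²), so 1 − 1.386/√3.921 = **0.300**.
- Half of these rejections point each way: 0.150 falsely favour the programme, against 0.025.
- Coverage of a nominal 95% interval: 1 − 0.300 = 70%.

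Neither the ICC nor the number of pupils enters this result, so more pupils per school do not repair it. Simulated GEE fits with no true effect (600 runs per setting, ICC 0 to 0.05) gave 0.26 to 0.34 with equal schools. With schools of 30, 70, 40 and 80 children they gave 0.31 to 0.38 (independence) and 0.41 to 0.55 (exchangeable).

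**3. GEE grouped by child, school ignored.** Design effect = 1 + (54 − 1) × ICC; type I error = 2P(Z > 1.96/√design effect).

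| Assumed ICC | Design effect | Type I error |
|---|---|---|
| 0 | 1.00 | 5.0% |
| 0.005 | 1.27 | 8.1% |
| 0.01 | 1.53 | 11.3% |
| 0.02 | 2.06 | 17.2% |
| 0.05 | 3.65 | 30.5% |

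**4. Corrections under school grouping, k = 2.**

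| Variance | Reference | Type I error |
|---|---|---|
| Unbiased (Kauermann-Carroll type) | normal | 18.9% |
| Mancl-DeRouen type | normal | 10.9% |
| Uncorrected sandwich | t, 2 df | 9.3% |
| Unbiased | t, 2 df (critical value 4.30) | 5.0% |

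A permutation test has C(4,2) = 6 allocations, so its smallest two-sided p is 2/6 = 0.33.

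**5. Power of the valid 2-df test for 0.2 kg/m².** Assume SD 0.434 and 54 children per school, so SE = 0.434 × √(2 × design effect/108). At ICC 0 the SE is 0.059 and the noncentrality 0.2/0.059 = 3.39. The noncentral t on 2 df with critical value 4.30 gives power of about 46%. At ICCs of 0.01, 0.02 and 0.05 it gives about 34%, 28% and 18%.

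**The case against.** The strongest reply is that the article names only GEE, and that the grouping unit, variance correction and reference distribution commonly belong in an analysis plan that is not shown. This stands as far as the figure goes. A reader might infer that the trial has a false-positive rate of 30%. The documents do not support that, because the rate rests on choices they do not state, and other choices give anything from 5% to above 30%. It does not remove the point. Four schools, GEE and alpha 0.05 are fixed in the protocol, and of the corrections checked only an unbiased variance with a 2-df reference restores 5%. That is a materially different test from the one whose power is stated.

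Four further limits also stand:

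- A reader might infer that about one in three ineffective programmes would be declared effective. The 30% is two-sided, so the rate of false benefit is about 15%.
- A reader might infer that standard errors are too small under every grouping. Under child grouping this needs an ICC above zero. At ICC 0 the test is correct, and the document gives no ICC.
- Planned data analyses specifies p-values and a significance level but no confidence interval. The 70% coverage applies to any interval that might be reported, not to one that is promised.
- The offer to control schools depends on the programme proving effective. Neither place that mentions it ties it to this p-value.

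**Conclusion.** The concern holds in conditional form. As written, the plan pairs four randomised schools with GEE at alpha 0.05, and standard GEE does not deliver that error rate. Under ordinary school-grouped robust GEE the two-sided error is about 30%, with about 15% falsely favouring the programme. This assumes an uncorrected sandwich variance, a normal reference and similar school sizes; in the simulations unequal sizes gave the same or worse. Under child grouping the error runs from 5% at an assumed ICC of 0 to about 30% at 0.05. The nominal rate is met only if the ICC is essentially zero in the child-grouped version, or if a full 2-df correction is used. Because this affects the primary inference, it should be changed before the data are analysed.

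**What to change.** Base the primary inference on the school as the unit:

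1. Regress each child's month-9 BMI on baseline BMI without the arm, and average the residuals within each school.
2. Compare the two intervention schools with the two control schools by a t test on 2 df, with a 95% confidence interval (multiplier 4.30).
3. Draw the conclusion from the estimate and interval.

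A GEE grouped by school with an unbiased small-sample variance and a t reference on 2 df is an acceptable equivalent. Uncorrected GEE may remain as a description only. Any secondary outcome analysed by GEE needs the same treatment.

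The change needs new analysis wording and no new data, but it has real costs. The interval becomes much wider. The stated 90% power no longer applies and must be restated; step 5 shows how far it falls under an assumed SD. The 2-df test relies on approximate normality of four school means, which cannot be checked, and a permutation test cannot replace it at the 0.05 level. The underlying limit is the number of schools: no analysis of two per arm recovers the planned precision, and only more schools would do so, if recruitment still allows.

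### The Wilcoxon test named for the secondary outcomes is not a valid between-arm comparison, in either of its forms, in a trial that randomises four schools

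*Protocol article*

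**What the plan says.** On the design, the Overview section states: "The units of observation are individual children, and the units of randomization are schools". The Randomization section specifies "distribution of two schools for the control group and two schools for the intervention group", so there are four clusters in all. The study design text below Figure 1 lists the outcomes that matter here: "the secondary outcomes are behaviors related to healthy eating, increased preferences for fruits and vegetables, increased physical activity and reduced screen time".

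The Planned data analyses section gives these outcomes two analyses in consecutive sentences. The first is "Adjusted analysis for primary and secondary outcomes will be performed using generalized estimating equations (GEE". The second is "The comparison between secondary outcomes will be performed using the nonparametric Wilcoxon test". It does not say whether the Wilcoxon test is the rank-sum or the signed-rank form, and it mentions no clustered version and no school-level summary. The same section sets a 0.05 level for every test.

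**The concern.** Children in one school share teachers, meals, neighbourhood and the delivery of the programme, so their outcomes tend to be correlated. A test that counts each child as an independent unit understates the variance of the difference between arms and rejects too often. With only two schools per arm, an ordinary difference between schools can pass for an effect of the intervention.

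The secondary outcomes carry much of the behavioural case for the programme. Among the benefits that the abstract expects are more fresh food and fewer sedentary hours. The abstract also counts physical activity as part of the primary outcome, although the study design text makes it secondary. If the article's conclusions on these behaviours rest on the Wilcoxon p-values, the stated 5% error rate does not apply to them.

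This is not a detail left for the SAP. The article names a specific test, and the test does not fit the article's own unit of randomisation.

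**Working it through.** **Inputs from the protocol article**
- Two schools per arm (Randomization).
- 99 children per group, increased by 10% for losses (Sample size).
- Alpha 0.05 (Planned data analyses). Two-sided testing is assumed, because the article does not say.

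**Assumptions**
- Schools of equal size. This gives 99/2 = 49.5 children per school, or 99 × 1.1 ≈ 109 per group and 109/2 = 54.5 per school with the increase.
- ICC from 0.01 to 0.10, because the article gives none.

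**The plan's own figure.** The article states no error rate for the Wilcoxon test. Its only related figure is 99 per group, and this does not reproduce. The inputs are given as "detect a difference in 0.2 kg/m^2^ on BMI, with a standard deviation of 0.05", with 90% power:

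n = 2 × (1.960 + 1.282)² × 0.05² / 0.2² ≈ 1.3, so 2 per group.

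A result of 99 needs an SD of about 0.2 × √(99/2) / 3.242 ≈ 0.434. That is a separate defect. Here 99 serves only to set the school size.

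**If the rank-sum form is meant.** With m children per school, the design effect is DE = 1 + (m − 1) × ICC. A test that ignores school has actual type I error of about 2 × [1 − Φ(1.96/√DE)]. For example, with m = 49.5 and ICC 0.02, DE = 1 + 48.5 × 0.02 = 1.97, and 2 × [1 − Φ(1.96/1.404)] = 16.3%.

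| Assumed ICC | DE, m = 49.5 | Error, m = 49.5 | DE, m = 54.5 | Error, m = 54.5 | Simulated rank-sum, m = 50 |
|---|---|---|---|---|---|
| 0 | 1.00 | 5.0% | 1.00 | 5.0% | 5.0% |
| 0.01 | 1.49 | 10.8% | 1.54 | 11.4% | 10.5% |
| 0.02 | 1.97 | 16.3% | 2.07 | 17.3% | 16.1% |
| 0.05 | 3.43 | 29.0% | 3.68 | 30.7% | 28.8% |
| 0.10 | 5.85 | 41.8% | 6.35 | 43.7% | 41.9% |

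The last column comes from 20,000 simulated null trials per ICC, with normal data and two schools per arm. A separate simulation with 54 children per school (4,000 trials per ICC) gave 4.9%, 10.9%, 16.2% and 29.3% at ICC 0, 0.01, 0.02 and 0.05.

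**If the signed-rank form is meant.** Measurements are taken at month 1 and month 9 (Assessments), so a paired test is possible. It asks whether children in one arm changed. Children grow and seasons change over that period, so a significant change in one arm and not in the other is no test of the difference between arms. The error rates in the table do not describe this form.

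**Would the GEE alone be enough?** Take the balanced case without covariates. The uncorrected robust variance divides the squared deviations of the two school means in each arm by 4. The unbiased variance of an arm mean is twice that. Comparing the uncorrected ratio with 1.96 therefore amounts to comparing a t statistic on 2 df with 1.96/√2 = 1.386. For 2 df, P(|T| > t) = 1 − t/√(2 + t²) = 1 − 1.386/√3.921 = 0.30. The simulation agrees, with 29.8% to 30.5% at every ICC. The school-level t-test on 2 df gave 4.9% to 5.2% at every ICC.

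**Would a permutation test of schools help?** There are 6 ways to split four schools two against two, so the smallest two-sided exact p-value is 2/6 = 0.33. Such a test could never reach 0.05.

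**The case against.** The strongest reply is that the article already assigns GEE, which can handle clustering, to the same outcomes. Because the GEE is called the adjusted analysis, the Wilcoxon test may be only its unadjusted companion, or a paired test of change within each arm. This is plausible, and it limits what can be claimed:

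- A reader might infer that the plan fixes a child-level rank-sum comparison of the arms. The text names no form, so the inflated error rates hold only if that form is meant.
- A reader might infer that the secondary outcomes would be tested only by an invalid method. The GEE sentence rules that out.
- A reader might infer that the authors are free to pick the more favourable of two results. The order of adjusted and unadjusted analyses is commonly left to a SAP or full protocol, neither of which is shown, so its absence here is no finding.
- A reader might infer that the authors predict benefit on all the secondary outcomes. The abstract's expected results do not name preference for fruit and vegetables or physical activity.

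The size of the inflation also depends on an assumed ICC and on equal schools. What the reply does not do is make the Wilcoxon test a valid comparison of arms. An unadjusted companion would still ignore school, and the GEE as described has its own problem with four clusters.

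**Conclusion.** The point holds as a defect in a stated rule. The article names a test for comparing secondary outcomes, and neither standard form of it gives a valid between-arm comparison when four schools are randomised. For the rank-sum form, the direction of the error is certain for any positive ICC. Its size is about 11%, 16% and 29% at ICCs of 0.01, 0.02 and 0.05, given about 50 to 54 children per school and equal schools. For the signed-rank form there is no between-arm test to assess.

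The 30% figure for the GEE assumes an uncorrected robust standard error with a normal reference. The article does not say which standard error will be used, so this is a reason to specify the correction and does not show that the planned GEE is wrong.

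**What to change.** Replace the Wilcoxon sentence in Planned data analyses, before outcome data are compared by arm:

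1. Remove the Wilcoxon test as a between-arm comparison. If a within-arm pre/post test or a child-level Wilcoxon test is kept, label it descriptive only.
2. Base inference for each secondary outcome on one named analysis that respects the school and is valid with four schools. One option is a school-level comparison of means, or of mean ranks for skewed or ordinal outcomes, with t on 2 df. The other is the planned GEE with a stated small-sample correction. In the balanced case without covariates, that correction has to address both the variance and the reference distribution, because both contribute to the 30%.

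The school-level option would be new to this protocol, which assigns the primary outcome to GEE as well. The same choice should therefore be considered there.

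The cost is one sentence in the plan and no new data. The statistical price is real: the critical value rises from 1.96 to about 4.30, a factor of 4.30/1.96 ≈ 2.2, before the standard error itself grows to reflect variation between schools. Intervals for the secondary outcomes will be much wider, which reflects the information that four schools can provide.
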